### Electrocardiogram, two-dimensional transthoracic echocardiogram, 24-hour Holter and blood pressure

All analyses will be performed annually by Lapclin-Chagas (INI), by qualified professionals. The 12-lead electrocardiogram will be conducted with patients at rest, using a long recording on D2 to assess arrhythmias. The presence or absence of electrocardiographic changes will be determined according to the criteria recommended by the II Brazilian Consensus on Chagas Disease [15]. Electrocardiographic analysis will be performed using the Holter system (portable three-channel recorder and analyzer; Cardio Light® and CardioSmart® 5.0, Cardio System, São Paulo, Brazil), with three channels connected continuously for 24 hours at a rate of 200 samples per second, to detect arrhythmias predictive of mortality and to obtain the arrhythmogenic profile [29,30]. Two-dimensional transthoracic echocardiography will be performed using a phased-array ultrasound system (Philips CVx, USA) equipped with an M4S transducer, following the recommendations of the World Heart Federation [31]. Left ventricular systolic ejection fraction (LVEF), as well as left ventricular diastolic and systolic volumes, will be quantified using Simpson’s biplane method of discs. Assessments will also include left ventricular diastolic function, right ventricular (RV) systolic function, and strain parameters of the left atrium (LA), RV, and left ventricle (LV), to provide a comprehensive evaluation of cardiac mechanics. All measurements will be performed by experienced cardiologists blinded to the clinical data to minimize bias. Blood pressure will be measured on the left arm with participants seated in a quiet room after 5 minutes of rest, using an Omron digital sphygmomanometer.

### Sample size

A minimum sample size of 90 volunteers was estimated, with 45 using AMIO and 45 not using AMIO. The sample size calculation for the primary endpoint was based on a study by Rodriguez-Angulo et al., 2017 [26] which evaluated differences in inflammatory markers in individuals with CD treated with AMIO (IFN-γ: 43.75 ± 24.83; TNF-α: 27.08 ± 13.81) compared to untreated individuals (IFN-γ: 84.37 ± 35.08; TNF-α: 52.08 ± 23.38). For the secondary endpoint, sample size calculation was based on a study by Saraiva et al., 2022 [22], which compared LVEF at different stages of CCC (LVEV; Stage A: 68.0 ± 6.4; Stage B: 54.7 ± 9.1; Stage C: 36.7 ± 10.7). Sample size calculations assumed a two-sided significance level of α = 0.05, a statistical power of 80% (1 − β = 0.8), and standard deviations and mean differences derived from these studies. The largest sample requirement among the two endpoints was adopted, and the sample size was increased by 20% to account for potential losses or refusals, resulting in a total of 90 participants.

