### Study design

This is a mixed (retrospective and prospective) longitudinal observational study designed to evaluate the association between chronic use of amiodarone (AMIO) and the following:

(I)**Primary outcome:** inflammatory profile, serologic reactivity to anti-*T. cruzi* antibody, and parasitic load;(II)**Secondary outcomes:** cardiovascular events (new sustained atrial arrhythmias, new sustained or non-sustained ventricular tachyarrhythmias, stroke, heart failure, atrioventricular block, and cardiovascular hospital admissions), CCC progression, internal cardioverter-defibrillator (ICD) implantation, heart transplantation, all-cause death, and a composite endpoint (including the aforementioned cardiovascular events, disease progression, ICD implantation, heart transplantation, and death).

Patients with CCC who take AMIO (exposed group) will be compared with those who do not take this drug (non-exposed group). To minimize potential confounding, patients will be matched based on the stage of CCC according to the Brazilian Consensus on Chagas Disease (A and B1 *versus* B2 and C), age (<50 years *versus* >50 years), and sex (female *versus* male) [15].

Clinical and laboratory data including blood tests, ECG, transthoracic two-dimensional echocardiography (ECHO), and 24-hour Holter monitoring, will be evaluated at three different time points:

(i)**Retrospective data**: from up to 3 years before the start of the study;(ii)**Baseline/recruitment**: at the time of inclusion in the study;(iii)**Prospective data**: during the 2 years of follow-up after recruitment;

The duration of the study, totaling five years of clinical follow-up, was established considering the CCC progresses at a rate of approximately 2% per year [22]. At recruitment, blood samples will be collected for biochemical and molecular analyses to obtain information related to the study’s primary outcome (Table 1) (Fig 1).

**Table 1 pone.0347305.t001:** AMIO-CHAGAS’s study Chronogram: Enrollment, Interventions and Outcome Assessments.

			Retrospective data	Recruitment	Prospective data
			2020 −2022	2023 - 2025	2025 - 2027
**Primary outcome:**	**Immunomodulatory effect**	Gene expression of CCC progression biomarkers in PBMCs	**–**	**x**	**–**
		Determination of serum levels of cytokines and nitric oxide	**–**	**x**	**–**
	**Trypanocidal effect**	Determination of anti-*T. cruzi* antibody titers	**–**	**x**	**–**
		*T. cruzi*-antigen quantification	**–**	**x**	**–**

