### Statistical analysis

Descriptive statistics were used to summarize the characteristics of the study population. Continuous variables will be presented as medians and interquartile ranges (IQR), and categorical variables as absolute and relative frequencies. Missing data will be assessed for their pattern and mechanism (i.e., missing completely at random (MCAR), missing at random (MAR), or missing not at random (MNAR)). The primary approach to handling missing data will be determined once the dataset is available. Depending on the extent and nature of missingness, appropriate strategies may include multiple imputation, complete case analysis, or sensitivity analyses to evaluate the robustness of the findings. The Shapiro-Wilk test will be used to assess the normality of continuous variables. When distributions deviate from normality, appropriate transformations or non-parametric tests will be applied.

Comparisons of patient characteristics according to AMIO use will be evaluated using the independent Student’s t-test for normally distributed continuous variables or the Mann-Whitney U-test for non-normally distributed data. Categorical variables will be compared using the chi-square test or Fisher’s exact test, as appropriate. Correlations between continuous variables related to the primary outcome will be assessed using Pearson or Spearman correlation coefficients, depending on data distribution. AMIO use and longitudinal changes in continuous variables will be analyzed using mixed linear models, adjusted for the duration of amiodarone use. Analyses of time course outcomes (e.g., cardiovascular events, disease progression, all-cause mortality) will be conducted using Cox proportional hazards regression models adjusted for potential confounders such as age, sex, comorbidities and previous etiologic treatment. Hazard ratios (HRs) and their 95% confidence intervals (CI) will be reported. A two-sided p-value ≤ 0.05 will be considered statistically significant.

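### The 80% power for the secondary endpoint rests on LVEF differences between disease stages, which gives no power for the listed event endpoints; for progression, the protocol's own rate implies only about 4 to 9 events

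*Protocol article*

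**What the plan says.** All references are to the Protocol article.

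- **Sample size:** "A minimum sample size of 90 volunteers was estimated, with 45 using AMIO and 45 not using AMIO". The primary endpoint is sized on IFN-γ and TNF-α in treated and untreated patients. The secondary endpoint is sized on a study "which compared LVEF at different stages of CCC", with LVEF of 68.0 ± 6.4 (stage A), 54.7 ± 9.1 (B) and 36.7 ± 10.7 (C). Both calculations use two-sided α of 0.05 and 80% power. The larger requirement is taken and raised by 20%.
- **Study design and Table 1:** the secondary outcomes are cardiovascular events, progression of chronic Chagas cardiomyopathy (CCC), ICD implantation, heart transplantation, all-cause death and a composite. Users and non-users of AMIO are matched on stage group (A/B1 against B2/C), age group and sex.
- **Study design, on duration:** the five years are justified by "considering the CCC progresses at a rate of approximately 2% per year".
- **Statistical analysis:** time-to-event outcomes, with cardiovascular events, progression and death as examples, go into Cox models "adjusted for potential confounders such as age, sex, comorbidities and previous etiologic treatment". Longitudinal continuous variables go into mixed linear models.

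**The concern.** A power statement should concern the endpoint and the contrast that will be tested. Here both differ. The endpoint sized is a continuous echo measure, while the listed secondary endpoints are events. The contrast sized is between disease stages, while the study compares AMIO users with non-users, and matching on stage group is meant to reduce stage differences between them. Gaps of 13.3 points (A to B) and 18.0 points (B to C) say nothing about the size of an AMIO effect.

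At stake is how the hazard ratios will be read. A reader who sees 80% power stated for the secondary endpoint may take a non-significant hazard ratio for progression as informative, when the expected events could hardly show anything short of an extreme effect. An adjusted model fitted to a handful of events can also give unstable estimates.

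**Working it through.** **1. The plan's own figure.** Inputs are the Sample size means and SDs, two-sided α 0.05 and power 80%. The formula is n per group = 2(1.960 + 0.842)² / d², where (1.960 + 0.842)² ≈ 7.85. The lower n uses the root-mean-square SD, the higher n the larger SD.

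| Contrast | Difference | d (root-mean-square SD) | n per group |
|---|---|---|---|
| IFN-γ | 84.37 − 43.75 = 40.62 | 1.34 | 9 to 12 |
| TNF-α | 52.08 − 27.08 = 25.00 | 1.30 | 10 to 14 |
| LVEF, A vs B | 68.0 − 54.7 = 13.3 | 1.69 | 6 to 8 |
| LVEF, B vs C | 54.7 − 36.7 = 18.0 | 1.81 | 5 to 6 |

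The largest requirement is 14 per group, 28 in total, or 34 to 35 after the 20% allowance (28 × 1.2 or 28 / 0.8). The stated 90 does not reproduce; it is larger than these inputs need. Two things follow. LVEF is not the more demanding of the two calculations, so removing it would not lower the requirement. And the IFN-γ and TNF-α comparisons are not underpowered on these inputs.

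**2. Expected progressions.** Inputs are 2% per year, 2 prospective years and 5 years in total (Study design), and 90 patients (Sample size). The rate is applied to both groups. Events = N × 0.02 × years.

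- 90 patients, 2 years: 90 × 0.02 × 2 = 3.6
- 90 patients, 5 years: 90 × 0.02 × 5 = 9.0 (8.6 with compounding, 90 × (1 − 0.98⁵))
- 75 retained (90 / 1.2), 2 years: 3.0
- 75 retained, 5 years: 7.5

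Nine is an upper figure. It counts all of the up to three retrospective years as time at risk. Study population requires only three months of AMIO at inclusion, so some of that time may be unexposed.

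**3. Power for progression.** The protocol gives no hazard ratio (HR), so these values are assumptions. Schoenfeld's approximation for equal groups: power = Φ(|ln HR| × √E / 2 − 1.96).

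- HR 0.5, E = 3.6: Φ(0.693 × 1.897 / 2 − 1.96) = Φ(−1.30) ≈ 10%
- HR 0.5, E = 9: Φ(0.693 × 3 / 2 − 1.96) = Φ(−0.92) ≈ 18%
- HR 0.3: about 23% with 4 events and 44% with 9

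Events needed for 80% power: 4 × 7.85 / (ln HR)². For HR 0.5 this is 4 × 7.85 / 0.480 ≈ 66; for HR 0.3 it is 22.

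With so few events the approximation is rough. It serves to show the order of magnitude, not exact percentages.

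**4. Events per parameter.** If AMIO and the four named example confounders take one parameter each, there are five: 3.6 / 5 ≈ 0.7 and 9 / 5 = 1.8 events per parameter.

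**5. The other endpoints.** The protocol states no rate for cardiovascular events, ICD implantation, transplantation, death or the composite, so no expected count can be derived. Table 1 marks ICD implantation, transplantation, death and the composite for the prospective period only.

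**The case against.** The strongest reply is that the article never claims 80% power for a hazard ratio. It attaches that figure to means and SDs. LVEF also has a place in the plan: Table 1 monitors progression by echocardiography among other tests, LVEF is among the collected continuous variables, and the mixed models can compare its course by AMIO use. This stands, and it narrows the point: the calculation does not cover the event endpoints. It does not rescue the calculation, because even for LVEF the difference used is between stages and not between AMIO groups.

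A reader might go further and infer that the whole Cox plan is unworkable. The documents do not support that. The 2% rate is for progression alone. Cardiovascular events include non-sustained ventricular tachyarrhythmia, atrioventricular block, heart failure and cardiovascular admissions, and will add events in unknown number. As an illustration only, 30 events would give about 48% power at HR 0.5.

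A reader might also take the five-parameter model as fixed. The confounders are introduced as examples, and the final set may be left to an analysis plan. The events-per-parameter figures are therefore conditional.

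Finally, the Discussion calls the study exploratory, and confidence intervals will show the imprecision. Both soften the consequence. Neither supports the stated power, and the article still sets a significance threshold of 0.05.

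**Conclusion.** The point holds in a limited form. The 80% power stated for the secondary endpoint concerns a stage contrast in LVEF, so it gives no power for any listed secondary endpoint. For progression the shortfall can be sized from the protocol's own rate: about 3.6 events over 2 years and at most about 9 over 5, or 3 and 7.5 with 75 retained. Power is then roughly 10% to 18% at HR 0.5, where about 66 events are needed. That is too few for a Cox model adjusted for several confounders.

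This rests on the 2% rate applying to the enrolled mix of stages, on equal groups and on an assumed HR. Power for cardiovascular events and for the composite cannot be judged either way. The primary cytokine comparison is not affected.

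**What to change.** - **Sample size:** delete the LVEF-by-stage basis and the 80% claim for secondary endpoints. State that the size rests on the cytokine endpoint and that the secondary endpoints are not powered. Since 90 exceeds what the cytokine inputs require, show how it was reached.
- **Progression, death, ICD implantation and transplantation:** report counts and rates by group with exact 95% CIs. For progression this follows from the event count. For the other three no rate is given; it is a cautious choice, given two prospective years of observation and the exclusion of stage D.
- **Cox regression:** reserve the adjusted model for all cardiovascular events or the composite, and limit the number of covariates to what the observed events support. A penalised or propensity-score model is one option among several.

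The cost is mainly text, with no change to recruitment or measurements. The downside is a less favourable power statement and no adjusted hazard ratio for the rare events.

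### The printed inputs give about 28 patients in total, not 90, so the stated basis for the sample size and its 80% power does not hold

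*Protocol article*

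**What the plan says.** The protocol article, Methods/Design, Sample size, sets out a full calculation:

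- Result: "A minimum sample size of 90 volunteers was estimated, with 45 using AMIO and 45 not using AMIO".
- Primary endpoint, from a published comparison of patients with Chagas disease on and off amiodarone: treated "IFN-γ: 43.75 ± 24.83; TNF-α: 27.08 ± 13.81"; untreated "IFN-γ: 84.37 ± 35.08; TNF-α: 52.08 ± 23.38".
- Secondary endpoint, LVEF by disease stage from a second published study: "Stage A: 68.0 ± 6.4; Stage B: 54.7 ± 9.1; Stage C: 36.7 ± 10.7".
- Error rates: "Sample size calculations assumed a two-sided significance level of α = 0.05", with 80% power.
- Source of the differences and standard deviations: the two cited studies. No other target difference is given.
- Final step: the larger of the two endpoint requirements was taken, and "the sample size was increased by 20% to account for potential losses or refusals, resulting in a total of 90 participants".

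The Statistical analysis section names the t-test, or the Mann-Whitney test for non-normal data, for comparing continuous variables between patients on and off amiodarone.

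**The concern.** The section presents 90 as the product of its own inputs, so the claim can be checked by arithmetic. The cited cytokine differences are larger than one standard deviation, and differences of that size need roughly ten patients per group, not the 36 to 38 per group that remain when the 20% is taken off 90.

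At stake is how the results will be read. A reader of this section will think that the study has 80% power only for differences as large as 40.6 units of IFN-γ or 25.0 units of TNF-α, and will take a null result to exclude only effects of that size. The Discussion criticises earlier amiodarone studies for having only 37 and 38 treated patients, so what this sample can detect is part of the study's own rationale.

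**Working it through.** **The stated figure, worked backwards.** If 20% was added, 90 / 1.2 = 75, or 37.5 per group. If 20% was allowed as a loss fraction, 90 × 0.8 = 72, or 36 per group. The stated inputs should therefore yield 36 to 38 per group before losses.

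**Method.** Two independent means, 1:1 allocation, two-sided α = 0.05, power 80%. Common SD = √((SD₁² + SD₂²)/2) and d = difference / common SD. The normal approximation is n per group = 2(1.960 + 0.842)²/d² ≈ 15.7/d². The last column uses the exact t-test.

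| Contrast | Difference | Common SD | d | n per group, normal | n per group, t-test |
|---|---|---|---|---|---|
| IFN-γ | 84.37 − 43.75 = 40.62 | √((24.83² + 35.08²)/2) = 30.39 | 1.34 | 9 | 10 (9.85) |
| TNF-α | 52.08 − 27.08 = 25.00 | √((13.81² + 23.38²)/2) = 19.20 | 1.30 | 10 | 11 (10.31) |
| LVEF, A vs B | 68.0 − 54.7 = 13.3 | √((6.4² + 9.1²)/2) = 7.87 | 1.69 | 6 | 7 |
| LVEF, B vs C | 54.7 − 36.7 = 18.0 | √((9.1² + 10.7²)/2) = 9.93 | 1.81 | 5 | 6 |
| LVEF, A vs C | 68.0 − 36.7 = 31.3 | √((6.4² + 10.7²)/2) = 8.82 | 3.55 | 2 | 3 |

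A one-way comparison of LVEF over the three stages needs 3 per stage, about 9 in total.

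**Applying the section's own rule.** The largest requirement is TNF-α, 11 per group or 22 in total. With the allowance this is 22 × 1.2 = 26.4, so 27, or 22 / 0.8 = 27.5, so 28. Against the stated 90, 90 / 28 ≈ 3.2.

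**Other readings, all on TNF-α:**

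- Larger SD (23.38) for both groups: 15 per group; 30 × 1.2 = 36 or 30 / 0.8 = 37.5, so 38 in total.
- Mann-Whitney (efficiency 0.864): 11 / 0.864 = 12.7, so 13 per group; 26 / 0.8 = 32.5, so 33 in total.
- Bonferroni over 20 tests (not stated): 20 per group; 40 / 0.8 = 50.
- 99% power (not stated): 23 per group; 46 / 0.8 = 57.5, so 58.
- Bonferroni over 20 tests with 95% power (neither stated): 29 per group; 58 / 0.8 = 72.5, so 73.

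Nothing at the stated error rates comes near 90. Getting close requires stacking assumptions that the section does not contain.

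**A possible origin.** Adding the two group SDs and using the sum as if it were the common SD gives 24.83 + 35.08 = 59.91, d = 40.62 / 59.91 = 0.678, n = 35.1, so 36 for IFN-γ. For TNF-α it gives 13.81 + 23.38 = 37.19, d = 25.00 / 37.19 = 0.672, n = 35.7, so 36. Then 36 / 0.8 = 45 per group, which is exactly 90. The sum of two SDs is not a pooled SD. The article does not say that this was done, so it is only an inference.

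**What 90 delivers.** For both cited cytokine differences, power exceeds 99.9% at 36 and at 45 per group. The standardised difference detectable with 80% power, and its value in cytokine units using the common SDs above, is:

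- 36 per group: d = 0.670; 0.670 × 30.39 ≈ 20 units IFN-γ; 0.670 × 19.20 ≈ 13 units TNF-α.
- 45 per group: d = 0.597; about 18 units IFN-γ and 11.5 units TNF-α.

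**The case against.** The strongest objection concerns LVEF. The printed values compare disease stages, whereas the study compares amiodarone with no amiodarone after matching on stage. The section does not say which LVEF difference was used, and a smaller one could have driven the larger requirement: with SDs of 6.4 to 10.7, a difference of about 4.3 to 7.2 points (0.67 × SD) gives 36 per group. It is right that stage differences are not the study's contrast. But no such smaller difference is printed, and the section says that its differences come from the cited studies. The only ones shown need the fewest patients, so this would explain 90 only by an input that the section omits.

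It can also be said that the error is harmless, because 90 is called a minimum, at least 80% power is met, and the study describes itself as exploratory. The direction is indeed safe and the study is not too small for the cited effects. That does not make the derivation correct: the text says that the calculation plus 20% results in 90 and mentions no discretionary increase.

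Finally, a detectable difference worked back from a fixed sample is not a justification, and 0.67 ignores multiplicity. This stands as a limit on the remedy. The primary outcome covers about 16 measures (six transcripts, seven cytokines, nitrate/nitrite, antibody, parasite load). Bonferroni over 16 would raise the detectable d at 36 per group to about 0.92.

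**Conclusion.** The concern holds. The stated inputs, error rates and selection rule give 11 per group and 27 to 28 in total, not 90. The statement that 90 results from them at 80% power is wrong by a factor of about 3.2, and no standard choice of formula at the stated error rates closes the gap. The fault lies in the justification, not in the adequacy of the sample: power for the cited cytokine differences is above 99.9%, and 80% power applies to differences about half as large.

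This rests on reading the printed ± values as standard deviations, as the section does, on equal groups, and on an unadjusted two-sample comparison. It also takes the printed LVEF stage differences as the LVEF inputs, since no others are given.

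**What to change.** Keep 90 and rewrite the Sample size paragraph:

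1. State the difference, standard deviation and formula that produced 90. If LVEF drove it, give the assumed difference between patients on and off amiodarone and its source. If no valid derivation exists, remove the claim that the cited means and SDs yield 90.
2. State what the sample provides: with 90 recruited and at least 36 evaluable per group, 80% power at two-sided 0.05 for a standardised difference of 0.67, about 20 units of IFN-γ or 13 units of TNF-α (0.60 if all 45 per group are evaluable). Describe this as the detectable difference for one unadjusted comparison, not as the reason for choosing 90.
3. Report power for the cited cytokine differences as above 99%, noting that those differences come from a single published study.
4. Say whether the 20% is a multiplier (× 1.2) or a loss fraction (/ 0.8).

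The cost is one rewritten paragraph. Enrolment, eligibility, endpoints and analysis do not change.

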### Statistical analysis

Descriptive statistics were used to summarize the characteristics of the study population. Continuous variables will be presented as medians and interquartile ranges (IQR), and categorical variables as absolute and relative frequencies. Missing data will be assessed for their pattern and mechanism (i.e., missing completely at random (MCAR), missing at random (MAR), or missing not at random (MNAR)). The primary approach to handling missing data will be determined once the dataset is available. Depending on the extent and nature of missingness, appropriate strategies may include multiple imputation, complete case analysis, or sensitivity analyses to evaluate the robustness of the findings. The Shapiro-Wilk test will be used to assess the normality of continuous variables. When distributions deviate from normality, appropriate transformations or non-parametric tests will be applied.

Comparisons of patient characteristics according to AMIO use will be evaluated using the independent Student’s t-test for normally distributed continuous variables or the Mann-Whitney U-test for non-normally distributed data. Categorical variables will be compared using the chi-square test or Fisher’s exact test, as appropriate. Correlations between continuous variables related to the primary outcome will be assessed using Pearson or Spearman correlation coefficients, depending on data distribution. AMIO use and longitudinal changes in continuous variables will be analyzed using mixed linear models, adjusted for the duration of amiodarone use. Analyses of time course outcomes (e.g., cardiovascular events, disease progression, all-cause mortality) will be conducted using Cox proportional hazards regression models adjusted for potential confounders such as age, sex, comorbidities and previous etiologic treatment. Hazard ratios (HRs) and their 95% confidence intervals (CI) will be reported. A two-sided p-value ≤ 0.05 will be considered statistically significant.

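### Groups are matched on stage group, age group and sex, but the named two-group tests ignore the matching; precision is lost to the extent that those factors predict a marker

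*Protocol article*

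**What the plan says.** **Design.** The Study design section states: "To minimize potential confounding, patients will be matched". The factors are stage group (A and B1 against B2 and C), "age (<50 years *versus* >50 years), and sex (female *versus* male"). The section gives no pairs, sets or matching ratio, so individual and frequency matching are both possible.

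**Sampling.** The same section and Table 1 place all primary-outcome measurements (gene expression, serum cytokines and nitric oxide, antibody, parasite quantification) at recruitment only.

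**Analysis.** The Statistical analysis section states: "Comparisons of patient characteristics according to AMIO use will be evaluated using the independent" t-test when a continuous variable is normally distributed, with Mann-Whitney otherwise. It adds: "Categorical variables will be compared using the chi-square test or Fisher’s exact test, as appropriate". Longitudinal changes in continuous variables "will be analyzed using mixed linear models, adjusted for the duration of amiodarone use". The Cox models adjust for confounders introduced by an open list that names age and sex but not stage.

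**Size.** The Sample size section states: "A minimum sample size of 90 volunteers was estimated, with 45 using AMIO and 45 not using AMIO".

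**The concern.** Matching gives the two groups the same make-up on the matched factors. If those factors predict a marker, part of the marker's spread is common to both groups and cancels from the difference in means. A test that treats the groups as independent samples leaves that part in its error term. It then rejects less often than its nominal level, and the precision that the matching could deliver is not used.

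The tests named are worded for patient characteristics, which is usual language for a baseline table. They still bear on the primary outcome. A marker measured once has no longitudinal change for a mixed model and no event time for a Cox model, and the planned correlations relate variables to each other rather than compare groups. Of the methods named, only the independent-sample tests can deliver the user versus non-user contrast.

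What is at stake is power and precision for modest effects. The Discussion faults two earlier null antiparasitic studies for having only 37 and 38 treated patients. With 45 treated patients here, avoidable loss of precision matters for the same question.

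**Working it through.** **1. Planned effects (Sample size section).**
- IFN-γ: difference 84.37 − 43.75 = 40.62; SD sqrt((24.83² + 35.08²)/2) = 30.39; standardised effect 1.34.
- TNF-α: difference 52.08 − 27.08 = 25.00; SD sqrt((13.81² + 23.38²)/2) = 19.20; standardised effect 1.30.

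At two-sided 0.05 and 80% power, n per group = 2 × (1.96 + 0.84)² / effect², which gives 9 for IFN-γ and 10 for TNF-α. The stated 90 in total does not follow from these inputs. That is a separate matter and does not affect this point. With 45 per group, the unmatched test has power above 99% for TNF-α, the smaller of the two effects.

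**2. Formula.** Let rho be the share of a marker's variance explained by the matching cells (2 × 2 × 2 = 8).
- Variance of the difference as an independent-sample test sees it: 2σ²/n.
- Actual variance when the groups share the same cell make-up: 2σ²(1 − rho)/n.
- Ratio of standard errors: 1/sqrt(1 − rho).

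**3. Size over a range of rho.** The protocol gives no rho for any marker, so the values below are assumptions. The simulation used 45 pairs sharing one of eight cells, nominal two-sided 0.05, a true difference of 0 or 0.5 SD, and 20,000 runs.

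| rho | SE ratio | Actual type I error, independent t | Power at 0.5 SD, independent t | Power at 0.5 SD, paired t |
|---|---|---|---|---|
| 0 | 1.00 | 0.050 | 65% | 64% |
| 0.1 | 1.05 | 0.040 | 66% | 69% |
| 0.2 | 1.12 | 0.032 | 67% | 73% |
| 0.3 | 1.20 | 0.020 | 68% | 79% |

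The paired test stayed near 0.05 throughout. In a separate simulation (4,000 runs), a linear model with the three factors as covariates had power of 69%, 74% and 80% at rho 0.1, 0.2 and 0.3. The gain therefore does not depend on analysing pairs.

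**4. What the protocol shows about rho.** Only LVEF can be examined, from its means and SDs by stage (A 68.0 ± 6.4, B 54.7 ± 9.1, C 36.7 ± 10.7). The stage mix is an assumption; stage B is split evenly between the two matching groups, and B1 and B2 are given the same mean.
- One third each of A, B and C. Group means: (2 × 68.0 + 54.7)/3 = 63.57 and (54.7 + 2 × 36.7)/3 = 42.70. Between-group variance: (20.87/2)² = 108.9. Average within-group variance: (94.2 + 175.9)/2 = 135.1. So rho = 108.9/(108.9 + 135.1) = 0.45.
- A, B1, B2 and C one quarter each: rho = 0.30.
- 10/40/40/10%: rho = 0.07.

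These values show that stage can matter, and that the amount depends heavily on case mix. They are for LVEF, not for a primary marker.

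**The case against.** **The tests may be meant only for the baseline table.** The wording fits that, and an article may leave the primary model to a fuller document. This stands in part: the link to the primary markers is an inference from single sampling and from the lack of any other named method. A reader should not infer that the protocol expressly assigns the t-test to the primary outcome.

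**The matching factors may explain little of a serum marker.** This stands. A reader might take the LVEF figures, or an assumed rho of 0.5 (simulated power 71% against 91%), as the likely loss. The protocol does not support that. LVEF measures ventricular function, is secondary, and is followed over time, so it falls to the mixed models. Nothing in the text puts a value on rho for cytokines, gene expression, antibody or parasite load. The stated purpose of matching presumes some relation to outcome, but not its strength.

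**Matching might seem to require paired tests.** It does not. Three dichotomies and sequential recruitment at routine visits fit frequency matching at least as well as pairs.

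**The error is conservative and the planned effects are large.** This stands. A reader might infer invalid or falsely positive results. The tests err the other way, and the crude difference stays balanced on the matched factors while the groups remain complete. Nor does the protocol promise over-wide confidence intervals for these comparisons, since it commits to intervals only for hazard ratios.

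What remains is that a stated design feature is not used by the named analysis, and using it costs almost nothing.

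**Conclusion.** The mismatch between the matched design and the named two-group tests is real, and its effect is conditional. For rho from 0.1 to 0.3, the unmatched standard error is about 5% to 20% too large, and the power forgone at 0.5 SD with 45 per group is about 3 to 11 percentage points. At rho = 0 nothing is lost. At the cytokine effects used for planning there is no practical loss of power, so the gain concerns smaller cytokine effects and the other primary markers.

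This rests on three assumptions: the independent-sample tests would be used for the primary markers, the matching is achieved as described, and rho lies in the range shown. The figures are for differences in means and do not carry over to the Cox models. The point is a free improvement in precision, not a threat to validity.

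**What to change.** In the Statistical analysis section:
- For the between-group comparison of continuous primary biomarkers, use a linear model on a suitable scale with amiodarone use, stage group, age group and sex. Where no transformation works, use the van Elteren test over the matching strata.
- For binary outcomes such as detectable parasite DNA, use Cochran-Mantel-Haenszel over the strata.
- Add the same three factors to the mixed models, and add stage group to the factors named for the Cox models.
- State whether matching is individual or by frequency. Use paired or conditional methods only if it is individual.
- Keep the independent t, Mann-Whitney, chi-square and Fisher tests for the descriptive baseline table.

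The cost is wording and about three model degrees of freedom (88 to 85 for the full 90 patients). The factors are already collected for the matching. Keeping them in the model also preserves adjustment if missing data disturb the matched balance.
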